One challenge observed during the single-arm pilot study was that 55% of participants were already engaging in psychological treatment, limiting our ability to attribute changes in PROMs solely to the effects of PRISM. Qualitative interview findings also suggested that the intervention could be of more value to those who were naive to psychological counseling. We determined that future research is needed to separate the effects of PRISM from those of CBT by excluding patients who are actively receiving CBT at the time of screening. We also intended to limit future studies to patients with mild or greater impairment due to pain in order to direct the intervention toward adolescents most in need, while increasing the possibility of demonstrating an improvement in functional disability scores. Lastly, to further assess the durability of PRISM, we planned to extend data collection beyond 3 months to include a 9-month follow-up survey. We also aimed to incorporate participant feedback from our single-arm pilot trial regarding overall helpfulness and benefits, reasons for deciding to participate, session logistics, accessibility, mental health perceptions, and caregiver interest in resilience into future protocols to better meet the needs of patients.

In this paper, we present the protocol for an ongoing pilot phase 2 randomized controlled trial (RCT) of PRISM for adolescents with CMP. The goal of this study is to determine whether the addition of PRISM to usual care demonstrates greater improvements in functional disability than usual care alone. Usual care was chosen as the comparator group to best mimic the clinical real-world setting and because denial of these services would not be ethically sound. Secondary aims include (1) determining the impact of PRISM on pain intensity and psychological distress, (2) exploring moderators of intervention effects, and (3) examining implementation outcomes of, facilitators of, and barriers to intervention engagement. This work provides the basis for a future definitive multicenter RCT to evaluate the efficacy of the intervention and feasibility of delivering resilience coaching across sites, as this will facilitate and support implementation of resilience coaching within usual care for CMP.

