### Control Group

This is the usual care group. This group will be assigned online questionnaires, as described earlier. Control group participants will not receive the PRISM intervention but will receive usual care. Although adolescent participants cannot be actively engaged in CBT at the time of enrollment, they will be allowed to start any type of mental health treatment recommended as part of their treatment plan for their CMP at any point during the study. Additionally recommended as part of usual care will be cardiovascular exercise and desensitization, which may include formal physical and occupational therapy. See Figure 3 for a comprehensive description of study visit activities and the timeline for both study arms.

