Furthermore, we will explore adolescent- and caregiver-level moderators of intervention effects, guided by an intersectionality framework [59]. For instance, we will investigate whether age moderates the intervention’s impact on functional disability by including the age × intervention interaction in the linear mixed effects regression model. If the interaction is significant, we will interpret it by plotting simple regression lines for younger (12-14 years) and older (15-16 years) adolescents. If PRISM proves more beneficial for younger participants, future studies may focus on this age group to maximize intervention effects. Additionally, we will evaluate whether biological sex moderates the intervention’s impact, ensuring adequate inclusion of male participants, given the predominance of females in the population with CMP [60].

Analyses will include calculation of eligibility, recruitment and attrition rates, and power considerations for the future full-scale RCT and evaluation of treatment fidelity. We will report the number of eligible subjects approached, the proportion of those subjects enrolled in the study, and the mean percentage of required sessions (PRISM 1-4 sessions + “coming together” session) attended among enrolled subjects. The study will be defined as feasible (binary) if the recruitment rate is ≥60%, the completion rate of all sessions among enrolled subjects is ≥70%, and the mean FIM score is ≥4. The intervention will be acceptable and appropriate if the mean AIM and IAM scores are ≥4 each. Intervention satisfaction (including session-specific and overall intervention satisfaction) will be reported as mean scores from the 5-point Likert scale (1=very dissatisfied to 5=very satisfied).

With a sample of 130 patient participants and an assumed ~20% attrition rate, we have more than 80% statistical power to detect a difference down to 5 points in the FDI between the intervention and control arms, given a prespecified mean FDI score of 26.9 (SD 11.8) and a significance level of .05 for the Student *t*-test. Table 1 lists the detectable differences (DDs) for the outcomes of interest, as well as the minimal clinically important difference (MCID) for each measure. The effect sizes of CBT on the FDI in similar patient populations have been strong to moderate (0.8-0.9), with between-group differences in the FDI score of 5.39 (95% CI 1.57-9.22). Therefore, we will be adequately powered for the primary outcome [61,62].

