### Conclusion

Findings from this work will further enhance our understanding of psychosocial factors that play an important role in adolescent CMP, with the goal of reducing the disease burden and improving long-term outcomes. A future multicenter RCT of PRISM for adolescents with CMP will provide further evidence of the efficacy of this program and inform clinical implementation. For some adolescents, the addition of PRISM to routine clinical care could offer sufficient pain-coping skills to reduce their need for individual counseling. For others, these learned skills may serve as a critical interim until formal CBT becomes available. Although PRISM would not fully solve issues such as clinic wait times, the integration of PRISM into clinical care could help prioritize the limited appointments in pediatric chronic pain clinics for those with the greatest need for interdisciplinary care.

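### The cited CBT effect does not support the statement that the trial is adequately powered: 5.39 FDI points has about 62% power at 50 evaluable per arm

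*Protocol article*

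**What the plan says.** All of the power statement is in the protocol article, Statistical Analysis, Quantitative Data, with Table 1.

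- For 130 randomized patients and roughly 20% attrition, the text says "we have more than 80% statistical power to detect a difference down to 5 points in the FDI between the intervention and control arms". The inputs named for this are an SD of 11.8 around a mean of 26.9, tested at "a significance level of .05 for the Student *t*-test". Table 1 gives the FDI detectable difference as 5.0 at 80% power with N=100, and its footnotes take the sample means from preliminary data.
- The text then turns to outside evidence: "The effect sizes of CBT on the FDI in similar patient populations have been strong to moderate (0.8-0.9), with between-group differences in the FDI score". It puts that difference at 5.39 points (95% CI 1.57 to 9.22). The next sentence is "Therefore, we will be adequately powered for the primary outcome". No PRISM effect size on the FDI is given.
- The trial compares PRISM plus usual care with usual care, allocated 1:1. Participants excludes only those currently receiving CBT. Under Control Group, the text says of adolescent participants that "they will be allowed to start any type of mental health treatment recommended as part of their treatment plan for their CMP at any point".
- The Introduction says future work should "separate the effects of PRISM from those of CBT by excluding patients who are actively receiving CBT at the time of screening". It names CBT as the most common mental health element of standard care and reports months-long waits for specialized pain care.

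**The concern.** The word that opens the adequacy sentence makes it a deduction from the CBT figures. Two things about that deduction need checking.

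The first is arithmetic: whether a 5.39-point difference, or a standardized effect of 0.8-0.9, gives adequate power with this trial's own SD and sample size.

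The second is transfer. The benchmark is for CBT. The trial tests a different, shorter program, added to a background in which patients may begin therapy after enrolment. If such therapy works and is taken up more in the control arm, or if PRISM adds little on top of it, the contrast at month 3 would be smaller than the benchmark.

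At stake is how a non-significant FDI result is read. A reader told that the trial was adequately powered would take it as evidence against PRISM more readily than the actual power allows.

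**Working it through.** **Inputs.** SD 11.8, alpha .05, Student t test, difference 5 points, 130 randomized with about 20% attrition (Quantitative Data); 100 evaluable (Table 1); 1:1 allocation (Recruitment and Randomization); 5.39 points and 0.8-0.9 (Quantitative Data). Sidedness is not stated, so two-sided is assumed. Note that 130 × 0.80 = 104, whereas 100/130 implies 23% loss; 50 and 52 per arm cover both.

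**Formula.** The noncentrality is δ / (SD × √(2/n)), and power comes from the noncentral t with 2n − 2 degrees of freedom.

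**Step 1: the plan's own figure (5 points, above 80%).** At n = 50 the standard error is 11.8 × √(2/50) = 2.36, and 5/2.36 = 2.12.

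| Evaluable per arm | Power for 5 points |
|---|---|
| 50 | 55% |
| 52 | 57% |
| 65 (no dropout) | 67% |
| 100 | 85% |

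The stated figure does not reproduce. A one-sided test gives 68% at 50 per arm and 78% at 65. An analysis adjusted for baseline would need a baseline correlation of about 0.65-0.7, but the stated test is unadjusted.

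**Step 2: Table 1 detectable differences at 80% power.**

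| Outcome (SD) | Table 1 | 50 per arm | 100 per arm |
|---|---|---|---|
| FDI (11.8) | 5.0 | 6.7 | 4.7 |
| Pain intensity (2.3) | 0.9 | 1.3 | 0.9 |
| K6 (6.0) | 2.4 | 3.4 | 2.4 |

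The pain and K6 entries equal the result for 100 per arm, so the total was probably entered as the group size. That is an inference; the document does not show its calculation.

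**Step 3: the CBT difference at face value.** At n = 50, 5.39/2.36 = 2.28.

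| Evaluable per arm | Power for 5.39 points |
|---|---|
| 50 | 62% |
| 52 | 64% |
| 65 (no dropout) | 73% |
| 77 | 80% |

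At 50 per arm, power is 10% at the lower confidence limit (1.57) and 97% at the upper (9.22).

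**Step 4: the standardized effect.** 5.39/11.8 = 0.46. On SD 11.8, 0.8-0.9 would be 0.8 × 11.8 = 9.4 to 0.9 × 11.8 = 10.6 points. To agree with 5.39 it would need an SD of 5.39/0.9 = 6.0 to 5.39/0.8 = 6.7. The two figures are therefore not on one scale here, and 0.8-0.9 says nothing about power for 5 points.

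**Step 5: dilution, as an assumption only.** Suppose a share p of the 5.39 points is lost through therapy started after enrolment. The document gives no value for p. At 50 per arm:

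| p | Contrast, 5.39 × (1 − p) | Power |
|---|---|---|
| 0% | 5.39 | 62% |
| 10% | 4.85 | 53% |
| 20% | 4.31 | 44% |
| 30% | 3.77 | 35% |

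If uptake is equal in both arms and the effects add fully, p is zero.

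**The case against.** A reader might go further and infer that the trial was sized on the wrong contrast, CBT versus no CBT, and that CBT in the control arm undermines the comparison. The documents do not support that, for these reasons:

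- The 5-point calculation is stated for this trial's own two arms, with a mean and SD from preliminary data. The CBT figures follow it as a check on plausibility and are not an input.
- The comparators in the CBT studies are not described. Their controls may also have been free to start therapy. Only the difference in active treatment is certain.
- No uptake rate is given. Nothing bars the PRISM arm from starting therapy too, and the reported waits may keep uptake low by month 3. The 55% in psychological treatment in the single-arm pilot was already being treated; current CBT is an exclusion here, so that figure does not inform new starts.
- The Conclusion's remark that, for some adolescents, "the addition of PRISM to routine clinical care could offer sufficient pain-coping skills to reduce their need for individual counseling" concerns later routine care and is not evidence of unequal uptake in the trial.
- The primary objective is already worded as PRISM with usual care against usual care alone, and the Introduction defends that comparator as the real-world one.
- The trial is meant to produce its own data for planning the larger study, so an inflated planning effect would not automatically be inherited.

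All of this stands, and it limits the transfer argument to a caution. It is also fair that the 0.8-0.9 may come from a study with a different SD, in which case the cited figures do not contradict each other at source. None of it rescues the adequacy sentence, because the 62% is the power with no dilution at all.

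**Conclusion.** The adequacy conclusion is wrong as written. The benchmark it rests on gives about 62-64% power at the planned evaluable sample, and the power stated just before it, above 80% for 5 points, is about 55-57%. These results assume a two-sided .05 unadjusted t test, SD 11.8 and 50-52 evaluable per arm. For scale, a true difference equal to the 8.0-point minimal clinically important difference in Table 1 would have about 92% power at 50 per arm, so the shortfall concerns differences of the size the text claims to detect. The corrected K6 detectable difference (3.4) exceeds the 3.0 listed there as clinically important; the pain value (1.3) stays below its 2.0.

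That the add-on contrast for PRISM could be smaller than a CBT effect is a reasonable caution of unknown size. The power range under dilution is illustrative and is not an estimate for this trial.

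**What to change.** In the power paragraph and Table 1:

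1. Remove the adequacy sentence, or restate it as about 62-64% power for 5.39 points with 50-52 evaluable per arm.
2. Correct the power for 5 points to about 55-57%, and the detectable differences at 50 per arm to about 6.7 (FDI), 1.3 (pain intensity) and 3.4 (K6). This must be done together with item 1; otherwise the paragraph would claim more than 80% for 5 points beside 62% for 5.39.
3. State whether the test is two-sided.
4. Remove 0.8-0.9, or label it as not on the SD 11.8 scale.
5. Say that the CBT effect is an external benchmark for PRISM added to usual care that may include newly started therapy. Show any dilution as an assumed range, for example 53%, 44% and 35% power if 10%, 20% and 30% of 5.39 points is lost.

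The cost is a few sentences and three table entries, and a less favourable stated power. Enrolment, data collection and patient care do not change.

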#### Qualitative Data

Semistructured interview findings will be used to understand barriers and facilitators to support future implementation of PRISM. Three team members will conduct the interviews after completing training on interview facilitation best practices. Research team members have a diverse experience spanning the domains of chronic pain, rheumatology, patient-centered care, and qualitative research methods and have varied levels of preknowledge of CMP. The principal investigator’s interpretation of interview findings will be informed by their expertise in treating adolescents with CMP, while several other team members have prior knowledge of CMP through their research work. To maximize reflexivity, the research team members will discuss their assumptions about the research topics and how these might influence their interpretation of findings both before and during data analysis.

Interviews with patients and caregivers will be transcribed verbatim. Two members of the study team will code transcripts independently and meet to identify emergent themes arising from a line-by-line review of narrative content, as well as a priori codes derived from the Consolidated Framework for Implementation Research (CFIR) and the Assessment, Decision, Adaptation, Production, Topical experts, Integration, Training and Testing (ADAPT-ITT) framework [63]. Next, 20% of interviews will be double-coded to insure intercoder reliability of the developed coding schema and enhance credibility of findings. Discrepancies will be resolved through consensus. Quantitative findings on efficacy and implementation outcomes will be synthesized with qualitative findings on facilitators of and barriers to engagement to support wide-based dissemination of PRISM in a multicenter RCT.

## Results

The trial is currently open. Initial IRB approval was obtained on April 21, 2023, and protocol version 4 was amended on January 14, 2025. Recruitment began on May 8, 2023, and we anticipate recruitment completion on August 1, 2025.

## Discussion

### Summary

This pilot RCT protocol is designed to assess whether the addition of PRISM to usual care is associated with greater improvements in functional disability compared to usual care alone. This intervention has the potential to enhance pain management and overall well-being for youth with CMP, who have been shown to have lower resilience than unaffected adolescents. The results of this study will heighten our understanding of the role of resilience over time and shed light on strategies that promote psychological resilience for patients with CMP and their caregivers. These insights will lay the groundwork for multicenter studies on the efficacy of PRISM in CMP and inform future treatment strategies for this population.

### Limitations

In terms of limitations of this protocol, it may be lacking in generalizability, as the population with CMP at our institution has been limited in racial and ethnic diversity. However, we do expect that our study sample will reflect the demographic makeup of patients with CMP within our clinic population. It is unclear based on the current literature whether our patient population aligns demographically with the population with CMP nationally. Our protocol is also limited to English-speaking participants. Offering PRISM in other languages would further increase the generalizability of future studies. Additionally, although pilot trial participants have approved of our flexibility in scheduling PRISM sessions outside of normal business hours, this may not be feasible in real-world clinical settings. Similarly, the 1-on-1 format of the intervention may be too time and resource intensive for routine clinical practice. This emphasizes the importance of future research to address these limitations and guide future implementation efforts.

### Conclusion

Findings from this work will further enhance our understanding of psychosocial factors that play an important role in adolescent CMP, with the goal of reducing the disease burden and improving long-term outcomes. A future multicenter RCT of PRISM for adolescents with CMP will provide further evidence of the efficacy of this program and inform clinical implementation. For some adolescents, the addition of PRISM to routine clinical care could offer sufficient pain-coping skills to reduce their need for individual counseling. For others, these learned skills may serve as a critical interim until formal CBT becomes available. Although PRISM would not fully solve issues such as clinic wait times, the integration of PRISM into clinical care could help prioritize the limited appointments in pediatric chronic pain clinics for those with the greatest need for interdisciplinary care.

## Appendix

Multimedia Appendix 1 SPIRIT (Standard Protocol Items: Recommendations for Interventional Trials) checklist.

Multimedia Appendix 2 Semistructured interview guide.

Multimedia Appendix 3 Peer-review report from AMS - Arthritis and Musculoskeletal and Skin Diseases Special Grants Study Section, National Institute of Arthritis and Musculoskeletal and Skin Diseases (National Institutes of Health, USA).

## Abbreviations

ACR: American College of Rheumatology
AHS: Adult Hope Scale
AIM: Acceptability of Intervention Measure
CAMM: Children and Adolescent Mindfulness Measure
CBT: cognitive behavioral therapy
CD-RISC-10: 10-item Connor-Davidson Resilience Scale
CHOP: Children’s Hospital of Philadelphia
CMP: chronic musculoskeletal pain
DSMB: data safety monitoring board
e-consent: electronic consent
EMR: electronic medical record
FDI: Functional Disability Inventory
FIM: Feasibility of Intervention Measure
FM: fibromyalgia
IAM: Intervention Appropriateness Measure
IRB: Institutional Review Board
K6: Kessler-6 Psychological Distress Scale
MCID: minimal clinically important difference
NIAMS: National Institute of Arthritis and Musculoskeletal and Skin Diseases
NIH: National Institutes of Health
PCS-C: Pain Catastrophizing Scale, Child report
PCS-P: Pain Catastrophizing Scale, Parent report
PGH-7: Pediatric Global Health 7
PRISM: Promoting Resilience in Stress Management
PROM: patient-reported outcome measure
PROMIS: Patient-Reported Outcomes Measurement Information System
PSAT: Pain and Symptom Assessment Tool
PSES-C: Pain Self-Efficacy Scale Child
RCT: randomized controlled trial
REDCap: Research Electronic Data Capture
SS: Symptom Severity
WPI: Widespread Pain Index
